**Fig. 3 Fig3:**
[figure not shown]
SPIRIT figure for the HU-FIX study. DASH Disabilities of the Arm, Shoulder and Hand, EQ-5D EuroQol Health Outcome, ROM range of movement, SF-12 12-item Short Form Health Survey, VAS visual analogue scale

### Primary outcome measure

The primary outcome measure is the DASH score at 3 months post-intervention. The DASH score is a functional rating scale that was developed in 1996. It has been used extensively as a research tool in upper limb surgery [28]. It consists of a 30-item self-reported questionnaire, and two optional modules, one assessing work and the other sports and performing arts. Patient symptoms (including pain, weakness, stiffness and tingling or numbness) and functional status (including physical, social and psychological aspects) during the week prior to survey completion are assessed. The final score is from 0 to 100, with 0 representing no disability and 100 the worst possible disability. A recent study demonstrated the DASH score to be both valid and reliable in evaluating outcomes in patients following a humeral shaft fracture [29].

The null hypothesis is that there is *no*
*difference* in early functional outcomes (DASH score at 3 months post-intervention) between the operative and non-operative management of patients following a humeral shaft fracture.

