## Background

Fractures of the humeral diaphysis (humeral shaft fractures) constitute 1.2% of adult fractures in the UK, with an overall incidence of 12.9 per 100,000 per year [1]. These injuries are more common in women and have a bimodal age distribution, with peaks of prevalence occurring in younger adults following high-energy trauma and older adults following low-energy trauma [1–3].

Humeral shaft fractures are routinely managed non-operatively, with the widespread use of a prefabricated humeral brace, as first described by Sarmiento et al*.* in 1977 [4]. The purported benefits of this technique (over conventional plaster immobilisation) include rapid and uninterrupted osteogenesis and early mobilisation of the shoulder and elbow, thus enhancing functional outcomes [4]. Subsequent studies comparing bracing with plaster immobilisation have demonstrated faster fracture union, reduced rates of varus mal-alignment and confirmed functional advantages in terms of shoulder and elbow mobility [5, 6].

Although functional bracing has resulted in low rates of humeral shaft fracture nonunion in some series [7–9], others have reported nonunion rates of 10% or more [10–13], with the highest rate reported as 33% [14]. When fracture union does occur, the reported time to union ranges from 7.5 to 11.5 weeks [7, 9], during which time almost all activities of daily living are restricted, and there is a risk of skin breakdown and secondary cellulitis that can necessitate brace removal [13]. Moreover, while malunion is considered to be tolerated well by patients, the acceptable thresholds are based upon an historic series of just 32 patients, who were examined by a single author [15]. A more recent series has suggested that malunion and consequent loss of shoulder range of motion can occur in up to 38% of patients treated with a brace [16].

The perceived limitations of humeral bracing have brought about a gradually increasing role for operative fixation [17]. Although intramedullary nailing is considered feasible, published case series [18], reviews [19, 20] and randomised controlled trials [21, 22] have consistently recommended open reduction and internal fixation (ORIF) as the strategy of choice when surgery is indicated.

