### Interventions

All patients will be initially treated in the Emergency Department with closed reduction of their humeral shaft fracture, and application of a either a U-slab or above-elbow hanging plaster cast.

Patients allocated to *operative* management of their humeral shaft fracture will undergo surgical fixation, using a standard technique of plating and screw fixation. The exact surgical approach and fixation technique utilised will be at the discretion of the treating surgeon. Similarly, post-operative immobilisation and range-of-motion restrictions will be at the discretion of the treating surgeon. This is determined by a number of factors including the injury and fracture pattern, bone quality, co-morbidities and patient compliance. The approach, fixation technique and range-of-motion restrictions will be recorded for all patients and presented as a sub-group analysis. Although the study sample will not be specifically powered on this basis (see Power calculation and statistical analysis, below), the investigators hope that a sub-group analysis will nonetheless allow any differences between the groups to be detected.

Patients allocated to *non-operative* management will be managed as per current standard practice for the study centre. This involves a period of immobilisation in a U-slab or hanging cast for up to 2 weeks, before fitting with a lightweight prefabricated humeral brace in the outpatient clinic. Two specific models of humeral brace are in routine use in this centre: the Clasby humeral brace (Beagle Orthopaedic, Blackburn, UK) and the ProCare over-the-shoulder humeral fracture brace (DJO Global, Vista, CA). The current standard of care in the study centre is to use the Clasby brace for proximal-third or mid-shaft fractures and the ProCare brace for distal-third or multifragmentary fractures. Brace selection for study participants will reflect these indications but will remain at the treating surgeon’s discretion. Patients will be permitted to start passive pendular shoulder exercises with full elbow, wrist and hand mobilisation as soon as the humeral brace has been applied. Post-injury physiotherapy will be arranged at the discretion of the treating surgeon, as occurs in everyday clinical practice.

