### Outcome assessment

All follow-up assessments will take place during outpatient clinic visits at 2 weeks, 6 weeks, 3 months, 6 months and 1 year. At each clinic visit, a physical examination will be performed, complications noted and the need for any further surgery recorded. Patients will be given time to complete a self-reported questionnaire, which will generate clinical outcome scores. The 1-year follow-up will enable study investigators to assess whether any differences between the operative and non-operative groups (if any) are sustained for 1 year post-intervention and to detect any important complications that may occur within the first year (e.g. nonunion).

The Standard Protocol Items: Recommendations for Interventional Trials (SPIRIT) [27] checklist is given in Additional file 1. The SPIRIT schedule of enrolment, interventions and assessments is shown in Fig. 3.

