### Power calculation and statistical analysis

Prior to study commencement, a prospective power calculation was used to determine the number of patients required in each treatment group. The minimal clinically important difference in the DASH score is reported to be 10 points [32], and the assumed standard deviation is 12 points for both the operative and non-operative groups [33]. Thus, using a two-sided *t*-test with 5% significance, a total of 70 patients (35 in each group) are required to produce a 90% power to detect a meaningful difference (in terms of the DASH score at 3 months post-intervention) between the two groups, assuming a 10% loss to follow-up.

Data will be analysed on an intention-to-treat basis. Data analysis will be performed by a senior statistician, employed by the local clinical research facility and independent of the study team. The primary outcome measure (DASH score at 3 months post-intervention) will be compared between the two treatment arms, using a two-sided independent samples *t*-test or non-parametric equivalent (as indicated by the normality of the data). This method will also be used to compare the other continuous outcome measures between the two treatment arms (e.g. pain score, satisfaction scores, shoulder and elbow range of motion, EQ-5D score and SF-12 score). The pattern of change in continuous outcome measures over the study period will be presented graphically, broken down by treatment allocation. A linear regression model will be generated for each participant by plotting the DASH score from 6 weeks to 1 year post-intervention and the gradient of the regression line (i.e. the rate of change in the score) will be compared between treatment groups. Multivariate linear regression, including analysis of covariance (ANCOVA), will also be used to adjust for the potential effect of pre-injury DASH score, age and other prognostic factors affecting the DASH score. Binary outcomes (e.g. treatment complications, re-operation and nonunion or malunion) will be compared between the two treatment arms using a binomial test for the comparison of proportions. Two-tailed *p* values will be reported where possible, and statistical significance will be set at *p* = 0.05.

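### The 3-month primary endpoint is timed from an arm-specific event that the article leaves undefined for the non-operative arm, so time since injury at assessment may differ between arms

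*Protocol article*

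**What the plan says.** - **Endpoint.** Under Primary outcome measure: "The primary outcome measure is the DASH score at 3 months post-intervention". The abstract, the study aim, the null hypothesis, the power statement, the primary analysis and the Missing data section use the same origin.
- **Operative arm.** The Inclusion criteria allow surgery up to 3 weeks after injury.
- **Both arms at presentation.** Under Interventions: "All patients will be initially treated in the Emergency Department with closed reduction of their humeral shaft fracture", followed by a U-slab or hanging cast. This comes before consent and allocation, which take place on the ward or at the first clinic appointment (Enrolment and allocation).
- **Non-operative arm.** Under Interventions: "a period of immobilisation in a U-slab or hanging cast for up to 2 weeks, before fitting with a lightweight prefabricated humeral brace".
- **Visits.** Under Outcome assessment: "All follow-up assessments will take place during outpatient clinic visits at 2 weeks, 6 weeks, 3 months, 6 months and 1 year". That list names no origin, although the same section describes the final visit as lasting to one year after the intervention, and the per-patient DASH regression is also timed from the intervention.
- **Analysis.** Under Power calculation and statistical analysis: "Data will be analysed on an intention-to-treat basis". The primary comparison is an unadjusted t-test or its non-parametric equivalent. The covariates named for the adjusted model are pre-injury DASH and age, with other prognostic factors unspecified. Time since injury is not named.

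**The concern.** Randomisation gives both arms a shared starting point. Counting from the intervention replaces it with an event whose nature and permitted delay depend on allocation. Surgery and brace fitting ordinarily come after allocation, and any wait for them is part of each strategy, yet this origin leaves the wait out of the follow-up clock. If the mean wait differs between arms, patients are assessed at different average times since injury, and the difference in healing time is mixed into the treatment effect.

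DASH asks about the preceding week, so the date of assessment can matter. With bracing, "the reported time to union ranges from 7.5 to 11.5 weeks", "during which time almost all activities of daily living are restricted". An assessment at about 13 weeks falls not long after the upper end of that range, when function may still be changing. Neither the primary test nor the named covariates would remove such an offset.

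There is also a practical gap. A patient allocated to surgery who never has it is kept in the operative group by intention-to-treat but has no surgical date from which to count 3 months.

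**Working it through.** **Inputs from the article.** Difference to detect 10 points; SD 12 in both arms; two-sided 5%; 90% power; 10% loss; 35 per arm. Surgery 0 to 3 weeks after injury; brace after 0 to 2 weeks in cast; cast at presentation.

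**Step 1. Reproduce the sample size.** n per arm = 2 × (1.96 + 1.2816)² × 12² / 10² = 30.3, rounded up to 31. Allowing for loss, 31 / 0.90 = 34.4, rounded up to 35 per arm, 70 in total. This matches the article. (The exact t distribution gives 32 evaluable per arm, then 32 / 0.90 = 35.6, so 36 per arm and 72 in total: a difference of two patients.) The time origin does not enter this formula.

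**Step 2. Time since injury at the 3-month visit.** Three months is about 91 / 7 = 13 weeks.

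| Arm and start | Start after injury (weeks) | Assessment after injury (weeks) |
|---|---|---|
| Operative, surgery | 0 to 3 | 13 to 16 |
| Non-operative, cast | about 0 | about 13 |
| Non-operative, brace | 0 to 2 | 13 to 15 |

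Operative minus non-operative, for individual patients:
- cast as start: 13 - 13 = 0 to 16 - 13 = +3 weeks;
- brace as start: 13 - 15 = -2 to 16 - 13 = +3 weeks.

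These are limits for individuals. The article gives no mean time to surgery or to brace fitting, so the mean offset between arms is unknown.

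**Step 3. Illustrative bias.** Two quantities are assumed, because the article gives neither: a mean offset of 0.5 to 1 week, and a DASH improvement near 3 months of 0.5 to 3 points per week. The value of 0.5 week is what results under the brace reading if starts are spread evenly over each window: 3/2 - 2/2 = 0.5.

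Bias = offset × slope. The smallest is 0.5 × 0.5 = 0.25 points; the largest is 1 × 3 = 3 points.

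**Step 4. Effect on the test.** With 10% loss, 35 × 0.9 = 31.5 evaluable per arm, and the standard error is 12 × sqrt(2 / 31.5) = 3.02. The results below use the noncentral t with 32 per arm (standard error 12 × sqrt(2 / 32) = 3.00). Power without bias is 90.7%.

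| Bias (points) | Type I error if no true difference | Power for a true difference of 10, bias opposing it |
|---|---|---|
| 0 | 5.0% | 90.7% |
| 0.25 | 5.1% | 89.2% |
| 1 | 6.2% | 84.0% |
| 1.5 | 7.8% | 79.7% |
| 3 | 16.6% | 63.2% |

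The normal approximation gives 17.0% for a 3-point bias. If the mean offset is zero, there is no bias.

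**The case against.** The strongest reply is that the brace is the natural start of non-operative care. The abstract describes that arm by its brace, and the study aim equates non-operative management with functional bracing. The initial cast goes to everyone before allocation and so does not distinguish the arms. On that reading the two windows, 0 to 3 and 0 to 2 weeks, largely overlap, and the mean offset could be near zero or of either sign. This stands, although Interventions also lists the cast period within non-operative care, so the cast reading is not excluded.

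A reader might infer more than the article supports:
- **That the arms are in fact compared at different stages of healing, to the advantage of surgery.** No waiting times are given. Only the cast reading makes the offset one-directional, with operative patients assessed later after injury.
- **That recovery is steep at 3 months.** The article gives no DASH trajectory. The quoted union times end before 13 weeks, which fits a flattening curve as well as a steep one.
- **That the full 3 weeks could serve as the bias between arms.** Three weeks is an eligibility limit. As a mean offset it would require every operation at that limit and every comparator patient starting on the day of injury.
- **That the origin contradicts intention-to-treat.** Intention-to-treat fixes the group in which a patient is analysed, not the clock. A braced patient who later has surgery still has a brace-fitting date. The gap concerns patients who never have their allocated operation.

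Finally, the SPIRIT figure and the full protocol (version 1.3) are not shown and may define the start. That limits confidence. But a definition that kept the intervention as origin would still depend on the arm.

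**Conclusion.** The point holds in limited form and should be fixed; confidence is medium. The article times its primary endpoint from an event that differs by arm and is not identified for the non-operative arm. The rule as written therefore permits unequal time since injury at the 3-month DASH, and patients who never have their allocated surgery have no time zero. For individual patients the difference can reach 3 weeks. Under the assumed mean offset and slope, the effect runs from negligible (0.25 points, type I error 5.1%) to material (3 points, about 17%). Those assumptions show scale only: bias is possible, not demonstrated.

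**What to change.** 1. Define the primary endpoint as DASH at 3 months from one origin common to both arms, preferably randomisation, since every participant has that date whatever treatment follows. Schedule the 2-week, 6-week, 6-month and 1-year visits from the same date, and time the DASH regression from it.
2. For patients already enrolled, record the dates of injury, randomisation, surgery, brace fitting and each DASH. Report time from injury and from randomisation to the 3-month DASH by arm.
3. Run a sensitivity analysis of the primary comparison that accounts for that time.

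The cost is a protocol amendment and minor rescheduling of visits. Some operative-arm visits will fall slightly earlier after surgery than under the current wording. The sample size stays at 70. The article projected enrolment until July 2020, so a change could still apply to patients recruited after its publication in August 2019. If the full protocol already fixes a common origin, the article's wording only needs to be aligned with it.

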### Secondary outcome measures

Secondary outcome measures will include:Change in the DASH score over the 1-year follow-up periodPain assessment, using a visual analogue scale (0 to 10)Complications of treatment, including neurovascular injury, superficial or deep infection, failure of fixation, revision surgery, skin complications (including eczema and cellulitis) and complex regional pain syndromeTime to return to work and sports (if relevant)Satisfaction with the service, using a visual analogue scale (0 to 100), and with the appearance of the affected limb, also using a visual analogue scale (0 to 10)Range of motion at the shoulder and elbowRadiographic assessment, using standard anteroposterior and lateral radiographs of the humerus to assess the progression of fracture healing (union or nonunion) and final humeral deformity (malunion)EuroQol (EQ-5D) health outcome score [30]12-item Short Form (SF-12) health survey score [31]Health economic analysis

Outcome measures 1 to 9 have been collated into a single data collection form (one form per study participant).

### Power calculation and statistical analysis

Prior to study commencement, a prospective power calculation was used to determine the number of patients required in each treatment group. The minimal clinically important difference in the DASH score is reported to be 10 points [32], and the assumed standard deviation is 12 points for both the operative and non-operative groups [33]. Thus, using a two-sided *t*-test with 5% significance, a total of 70 patients (35 in each group) are required to produce a 90% power to detect a meaningful difference (in terms of the DASH score at 3 months post-intervention) between the two groups, assuming a 10% loss to follow-up.

Data will be analysed on an intention-to-treat basis. Data analysis will be performed by a senior statistician, employed by the local clinical research facility and independent of the study team. The primary outcome measure (DASH score at 3 months post-intervention) will be compared between the two treatment arms, using a two-sided independent samples *t*-test or non-parametric equivalent (as indicated by the normality of the data). This method will also be used to compare the other continuous outcome measures between the two treatment arms (e.g. pain score, satisfaction scores, shoulder and elbow range of motion, EQ-5D score and SF-12 score). The pattern of change in continuous outcome measures over the study period will be presented graphically, broken down by treatment allocation. A linear regression model will be generated for each participant by plotting the DASH score from 6 weeks to 1 year post-intervention and the gradient of the regression line (i.e. the rate of change in the score) will be compared between treatment groups. Multivariate linear regression, including analysis of covariance (ANCOVA), will also be used to adjust for the potential effect of pre-injury DASH score, age and other prognostic factors affecting the DASH score. Binary outcomes (e.g. treatment complications, re-operation and nonunion or malunion) will be compared between the two treatment arms using a binomial test for the comparison of proportions. Two-tailed *p* values will be reported where possible, and statistical significance will be set at *p* = 0.05.

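### The observed normality of the 3-month DASH scores decides whether the primary comparison is a t-test or a rank test, but the trial is sized on a 10-point mean difference and no mean-difference analysis is fixed as primary

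*Protocol article*

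**What the plan says.** All main statements are in the protocol article, section Power calculation and statistical analysis, unless noted.

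- **Outcome** (section Primary outcome measure): "The primary outcome measure is the DASH score at 3 months post-intervention". The null hypothesis there is of no difference; it does not say whether a mean, a median or a rank quantity is meant.
- **Sizing:** "The minimal clinically important difference in the DASH score is reported to be 10 points", and "the assumed standard deviation is 12 points for both the operative and non-operative groups". The 70 patients follow "using a two-sided *t*-test with 5% significance" and 90% power, with 10% loss to follow-up.
- **Primary test:** an independent-samples t-test or a "non-parametric equivalent (as indicated by the normality of the data"). The article gives no criterion for normality and no effect measure for the non-parametric branch. The next sentence applies the same method to the other continuous outcomes.
- **Adjusted analysis:** linear regression including ANCOVA is planned in addition, adjusting for pre-injury DASH, age and other prognostic factors. It is not designated primary.
- **Analyst:** a senior statistician independent of the study team.

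**The concern.** The sizing fixes the question as a difference in mean DASH judged against 10 points. The analysis rule then lets the outcome data decide whether that question is the one tested. If the data look non-normal, the primary p-value comes from a rank test (Mann-Whitney is the natural reading of the non-parametric equivalent). That test asks whether scores in one arm tend to exceed those in the other. The two questions coincide only when one arm's distribution is the other's moved by a constant.

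The difference could matter here. DASH runs from 0 to 100 with 0 as no disability, so skew is plausible. The Background section notes of bracing that "others have reported nonunion rates of 10% or more", with a highest reported rate of 33%. The arms might therefore differ mainly through a minority of brace patients who do very badly. That pattern makes the data look non-normal, and ranks then give it less weight than means do.

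The planned ANCOVA does not settle the matter, because nothing says which result carries the conclusion if the rank p-value and the adjusted mean difference disagree.

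**Working it through.** **1. Reproduce the sample size.** Inputs from the article: difference 10, SD 12, two-sided 5%, power 90%, loss 10%.

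n per arm = 2 × (1.960 + 1.282)² × 12² / 10² = 2 × 10.51 × 1.44 = 30.3, so 31. Allowing for loss: 31 / 0.90 = 34.4, so 35 per arm and 70 in total. This matches the article. (The noncentral-t calculation gives 32 evaluable per arm, or 36 with loss and 72 in total, which is a trivial difference. Power at 31 per arm is 89.8%.) The sizing is for a difference in means.

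**2. Simulate the rule.** There are 31 evaluable patients per arm and 10,000 to 20,000 runs per scenario. These are assumptions, not figures from the article: the gamma shape, the means, the unequal SDs, the poor-outcome score, and the switching criterion (Shapiro-Wilk p < 0.05 in either arm). SD is 12 unless stated.

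*How often the rule switches to the rank test, and type I error, when both arms share a distribution:*

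| Distribution | Switches | Type I error under the rule |
|---|---|---|
| Normal | about 10% | 4.9% |
| Gamma, mean 20 | about 85% | 5.0 to 5.7% |
| Gamma, mean 30 | about 53% | 5.6% |
| Gamma, mean 40 | about 35% | 5.0% |

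The t-test's own type I error in these scenarios is 4.8 to 5.1%, so the switch does not repair a fault in the t-test.

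*Rejection when the means are equal but the spread differs:*

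| Scenario | Rank test | Welch's t |
|---|---|---|
| Gamma, mean 20, SD 10 v 14 | about 8% | about 5% |
| Gamma, mean 20, SD 8 v 18 | about 23% | about 6% |
| Gamma, mean 40, SD 8 v 18 | about 10% | about 5% |
| Normal, SD 8 v 18 | about 6% | about 5% |

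The excess comes mainly from skewed shapes that differ, not from unequal spread alone.

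*A minority of brace patients with a score of about 60, the rest matching surgery (gamma, mean 20):*

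| Poor outcomes | Mean difference | Rank test rejects | t-test rejects |
|---|---|---|---|
| 10% | 0.10 × (60 − 20) = 4 | about 10% | about 17 to 18% |
| 15% | 0.15 × (60 − 20) = 6 | about 16 to 17% | about 30 to 31% |

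*Power for a 10-point difference:*

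| Scenario | t-test | Rank test |
|---|---|---|
| Normal, 20 v 30 | 90% | 88% |
| Gamma, 20 v 30, SD 12 in both | 89% | 93% |
| Gamma, mean 20, pure shift of 10 | 90% | 94% |

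Under the switching rule itself, power is 90% in the normal case and 93% in the gamma 20 v 30 case.

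**The case against.** The best defence is that under the article's own assumption of equal SDs the rule does almost no harm. Type I error stays near 5 to 6%, power is about 90% for normal data, and under skew the rank test is the more powerful one. That stands.

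Other parts of the defence also stand in part:

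- **The magnitudes depend on assumptions.** The article gives no expected DASH mean, no unequal SDs and no DASH score for patients whose fracture fails to unite. Switching falls from about 85% to about 35% as the assumed mean rises from 20 to 40, so a reader cannot conclude that the t-test would usually be abandoned. The size must be read as a range.
- **The normality criterion may be in a full analysis plan.** Its absence from the article is no fault. The fault is the stated rule that the data choose the primary test, and a precise criterion would not remove it.
- **A mean difference is already planned.** ANCOVA is to be fitted in any case, and nonunion is compared separately as a binary outcome, so brace failures are not hidden. What remains is that no analysis of the mean difference is designated primary.

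Three stronger readings are tempting but unsupported. A reader might infer that the test is chosen by someone who sees the allocation. The article says that patients and assessors cannot be blinded, but it does not say so of the analyst, who is independent of the study team. A reader might infer that the trial is underpowered or its alpha inflated. The stated 70 reproduces, and alpha holds when the arms share a distribution. A reader might also infer that a rank test misleads whenever spreads differ. With normal scores and SDs of 8 v 18 it rejects in only about 6% of trials.

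**Conclusion.** The point holds as one about the target of the primary analysis. The article sizes the trial for a 10-point mean difference, lets observed normality replace the test of that difference with a test of something else, and names no mean-difference analysis that prevails.

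Under the assumptions above (31 per arm, Shapiro-Wilk in either arm), its size is:

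- switching in about 10% of trials for normal data, and about 35 to 85% for gamma-shaped scores;
- with equal means and unequal, skewed spread around a mean of 20, rejection of about 8 to 23% by the rank test against 5 to 6% by Welch's t;
- with 10 to 15% of brace patients doing very badly, rejection of about 10 to 16% by the rank test against about 18 to 31% by the t-test.

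The sample size is sound. The severity is minor to moderate: the harm needs arms that differ in shape, which is plausible here but not shown by the article.

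**What to change.** For the primary outcome, delete the normality rule and name one analysis in advance that estimates the difference in mean 3-month DASH with a 95% confidence interval. The already planned ANCOVA, adjusted for pre-injury DASH and age group (the stratification factor), is the natural choice; Welch's t-test is the alternative. State that this result carries the primary conclusion whatever the distribution looks like, and keep the rank test as a named sensitivity analysis.

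The cost is about one sentence in the plan. N stays at 70 and no new data are needed. The downside is somewhat lower power if scores are skewed and the treatment effect is close to a constant shift: about 89 to 90% for the t-test against 93 to 94% for the rank test in the gamma scenarios with a lower mean of 20.

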## Methods/design

The Humeral Shaft Fracture Fixation (HU-FIX) Study is a single-centre prospective randomised controlled trial that aims to assess whether there is any difference in outcome between patients with a humeral shaft fracture who are managed operatively (i.e. with surgical fixation) and those managed non-operatively. The study will adhere to the principles in the latest Consolidated Standards of Reporting Trials (CONSORT) Statement [23]. The study will be performed at a large tertiary referral centre. The study received a favourable opinion from the relevant research ethics committee on 19 July 2018 (South-East Scotland Research Ethics Committee 01 reference 18/SS/0073). The study is sponsored by National Health Service (NHS) Lothian Research and Development and was approved on 10 September 2018 (project number 2018/0223). The study was registered with the ClinicalTrials.gov database, which is operated by the US National Library of Medicine, on 28 September 2018 (ID NCT03689335). The study is funded and co-sponsored by the Scottish Orthopaedic Research Trust into Trauma (SORT-iT).

The trial will include all eligible patients presenting to the study centre with an isolated closed fracture of the humeral shaft. The planned flow of patients through the study is as shown in Fig. 1.

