### Exclusion criteria

Completely undisplaced fracturesInjuries considered to be an absolute indication for surgery (including severe associated neurovascular injury, open fractures and bilateral injuries)Patients with a periprosthetic or pathological fracturePatients with an additional spine or limb injury (including those with polytrauma), which may impact upon functional rehabilitationPatients medically unfit for surgeryVery frail patients, defined as those with a Clinical Frailty Score of ≥6/9 as described in the Canadian Study on Health and Aging [25]Pregnant women with predetermined treatmentPatients declining operative managementPatients unable to comply with post-operative data gathering, including completing questionnaires in EnglishNon-residents or those unable to return to the Unit for the 1-year follow-up periodPatients for whom the treating surgeon does not feel that inclusion in the trial is in their best interests, either due to fracture pattern or patient factors

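### Shoulder and elbow motion is compared without any covariate; measuring the uninjured opposite arm once and adjusting for it would be a cheap gain in precision on a secondary outcome.

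*Protocol article*

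**What the plan says.** Under Secondary outcome measures, the protocol article lists motion at the shoulder and elbow, with no reference side and no scale. Under Power calculation and statistical analysis, the primary comparison is a two-sided independent-samples t-test or its non-parametric equivalent, and then: "This method will also be used to compare the other continuous outcome measures between the two treatment arms". The examples given are "pain score, satisfaction scores, shoulder and elbow range of motion, EQ-5D score and SF-12 score", so motion is named explicitly. The same section introduces multivariable regression and ANCOVA to "adjust for the potential effect of pre-injury DASH score, age and other prognostic factors affecting the DASH score". No adjusted analysis is described for motion.

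On the opposite arm, the Methods/design section describes the trial population as "all eligible patients presenting to the study centre with an isolated closed fracture of the humeral shaft". The Exclusion criteria remove "open fractures and bilateral injuries", and also additional limb injuries where these could affect rehabilitation. Measurement of the opposite arm is not mentioned anywhere. The Outcome assessment section already provides for a physical examination at each of the five clinic visits.

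**The concern.** Loss of motion is part of the trial's rationale: the Background cites it as a consequence of malunion after bracing, and the stated secondary aim includes shoulder and elbow motion. The quantity of interest is thus motion lost. An injured-side angle at follow-up combines that loss with the patient's own normal motion. Recruitment starts at age 16 with no upper limit, so normal motion can be expected to vary between patients, and that variation adds to the error of the comparison.

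The DASH analysis has a pre-injury score available as a covariate. Motion has no such value, because nobody measured the arm before it broke. The opposite arm is the natural substitute, and the eligibility rules leave it acutely uninjured in nearly all patients. What is at stake is the width of the confidence interval for a secondary outcome on which the trial was not sized.

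**Working it through.** **1. The plan's own figure.** Inputs from Power calculation and statistical analysis: DASH difference 10, SD 12, two-sided 5%, power 90%, 10% loss.

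- Normal approximation: n = 2 × (1.960 + 1.282)² × 12² / 10² = 30.3, so 31 per arm. Then 31 / 0.9 = 34.4, so 35 per arm and 70 in total. This reproduces the stated figure.
- Exact t-test: 32 per arm, 36 after allowance for loss, which is one more per arm than stated.
- 35 × 0.9 = 31.5, so about 31 or 32 patients per arm should be evaluable. I use 32.

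This calculation concerns the DASH only. The protocol has no corresponding figure for motion.

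**2. Assumptions for motion, none of them in the protocol.** SD of injured-side motion 20 degrees; true difference between arms 10 degrees; correlation r between injured and opposite side at follow-up, shown at 0.3, 0.5 and 0.7.

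**3. Formulae.**

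- Unadjusted comparison: residual SD = 20.
- ANCOVA on opposite-side motion: residual SD = 20 × √(1 − r²).
- Side-to-side difference, equal SDs on both sides: SD = 20 × √(2(1 − r)).
- 95% CI width = 2 × 1.96 × SD × √(2/32). Since √(2/32) = 0.25, this is 0.98 × SD.
- Power: two-sample t-test, two-sided 5%, 32 per arm, with the SD above.

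**4. Results.**

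| Analysis | r | Variance relative to unadjusted | SD (degrees) | 95% CI width (degrees) | Power |
|---|---|---|---|---|---|
| Unadjusted | – | 1.00 | 20.0 | 19.6 | 50% |
| ANCOVA | 0.3 | 0.91 | 19.1 | 18.7 | 54% |
| ANCOVA | 0.5 | 0.75 | 17.3 | 17.0 | 62% |
| ANCOVA | 0.7 | 0.51 | 14.3 | 14.0 | 79% |
| Simple difference | 0.3 | 1.40 | 23.7 | 23.2 | 38% |
| Simple difference | 0.5 | 1.00 | 20.0 | 19.6 | 50% |
| Simple difference | 0.7 | 0.60 | 15.5 | 15.2 | 72% |

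With 31 per arm, the unadjusted and ANCOVA powers are 49%, 53%, 61% and 77%.

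**5. Reading.** ANCOVA never increases the residual variance in this formula, and its only cost is one degree of freedom. Subtraction behaves differently: with equal SDs, 2(1 − r) exceeds 1 whenever r < 0.5, so it is then less precise than the injured-side value alone. If the opposite-side SD is half the injured-side SD, the relative variance is 1 + 0.25 − r, and subtraction helps only when r > 0.25.

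**The case against.** The strongest reply is that nothing here is an error. The arms are randomised 1:1 and stratified at age 65, so the difference in injured-side motion is an unbiased estimate of the treatment effect with or without a reference arm. That stands. A reader might infer that a stiff older patient who has recovered fully is counted as a failure. The protocol does not support this, since it sets no motion threshold and classifies no individual as a good or poor result.

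Second, the article does not say how motion is scaled. The named test could be applied to a side-to-side deficit, and the full protocol or the data collection form may specify one. That also stands: analysis of raw angles is inferred from silence. What the article does state is the between-arm test, and it describes adjustment for the DASH only.

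Third, it is tempting to say that every eligible patient has a sound opposite arm. That goes too far. The limb-injury exclusion is qualified, and earlier disease of the opposite shoulder or elbow is not listed as an exclusion, in a trial with a stratum aged 65 or over.

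Fourth, the gain depends on an unknown correlation. Healing, immobilisation and treatment all influence the injured arm during follow-up and may lower it; at r = 0.3 the gain is small. This limits the size of the benefit, but adjustment still loses essentially nothing.

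Finally, the Missing data section compares per-participant gradients for the variable of interest, in which a patient's constant level of motion cancels. Those gradients measure rate of recovery. They do not replace a reference for the motion attained.

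**Conclusion.** The point holds as a cheap improvement in precision on a secondary outcome. The only comparison of motion that the article describes has no covariate, no pre-injury value can be measured, and a usable reference exists in nearly every patient.

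Under the assumed SD and difference, the gain runs from slight (power 50% to 54% at r = 0.3) to considerable (50% to 79% at r = 0.7). Those figures illustrate a range and are not estimates from the trial. The calculation does not establish that the planned comparison is needlessly imprecise, because the protocol gives no correlation from which to judge. The direction of the gain is secure for covariate adjustment but not for simple subtraction. The primary outcome, the sample size and the validity of the randomised comparison are untouched.

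**What to change.** Measure the same shoulder and elbow movements once on the opposite arm, at a visit that already includes an examination, for example 6 weeks or 3 months. Compare the arms by ANCOVA on injured-side motion, with opposite-side motion and the age stratum as covariates. Report the side-to-side deficit in degrees descriptively only. If the full protocol or data form already records the opposite side, only the analysis sentence needs to change.

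Cost: a few minutes of measurement per patient, extra fields on the data collection form, and one sentence in the analysis plan. In patients with earlier disease of the opposite arm the reference is poorer; covariate adjustment tolerates this better than subtraction does.
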